### Data analysis

Data will be analysed using either STATA or R.
Table 2 outlines the planned data analyses stratified by the specific objectives of the study. Infant age at every sampling occasion and at every safety and developmental assessment will be recorded to the day. Both postnatal age (PNA) and postmenstrual age (PMA = gestational age at birth + PNA) will be derived for each timepoint and treated as time-varying variables. The population pharmacokinetic model (NONMEM/Monolix) will incorporate, as fixed structural features, allometric size scaling (exponent 0.75 on apparent clearance, 1 on volume of distribution) and a sigmoidal maturation function on apparent clearance, with PMA50 and the Hill coefficient set to published values for UGT1A1 ontogeny rather than estimated from this small cohort. Residual covariate effects of PNA, weight, sex, and feeding pattern will then be tested empirically. To probe the robustness of the maturation assumption, we will conduct a pre-specified sensitivity analysis re-fitting the model with at least one alternative published UGT1A1 ontogeny parameter set (1) and report the resulting impact on individual exposure estimates. Relative infant dose (RID) will be reported overall and by infant-age stratum (<9 months and 9–<12 months). Comparative growth and developmental analyses will use WHO z-scores and age-adjusted CREDI scores; longitudinal mixed-effects models will include infant age at measurement as a continuous covariate. Because exposure groups are self-selected, all comparative analyses are observational and exploratory. Primary safety results will be descriptive: counts, proportions with exact 95% confidence intervals, incidence rates, and Kaplan–Meier curves, without group-comparison p-values. Longitudinal growth and CREDI outcomes will be analysed with mixed-effects models adjusting for a minimal pre-specified set of covariates: infant age at measurement, infant sex, and site. Formal between-group inference for safety is deferred to other larger PK studies. Where feasible, we will perform sensitivity analyses to reduce imbalance, recognising limitations due to our sample size.

**Table 2. T2:** Planned data analyses aligned with study objectives in the CABMILK study.

Objective	Data analysis	Outcome
To profile the extent of CAB transfer in breast milk and determine its pharmacokinetics in infants whose mothers receive long-acting injectable cabotegravir for HIV preexposure prophylaxis (PrEP).	We will use non-linear mixed effects models to determine the compartmental pharmacokinetics of CAB from maternal plasma to breast milk to infant plasma. We will first calculate the milk: plasma ratio to determine the average milk CAB concentration compared with the average maternal plasma concentration. Second, we will utilise individual predicted infant CAB concentrations to calculate infant overall exposure (AUC0-∞) and estimate CAB infant half-life as well as elimination rate constant. Third, we will estimate the CAB dose ingested by each infant, through breast milk, relative to the maternal dose; the relative infant dose (RID). ^ 25 ^ This RID will allow us to determine the extent of CAB breast milk exposure that would result in attained concentrations in the infant’s blood that are above or below the protein-adjusted IC90 of 0.166 μg/mL. ^ 26 ^	CAB transfer to the infant through breast milk, and profile the attained infant concentrations.
To determine the association of breast milk CAB exposure and infant safety outcomes (growth pattern, neuro-cognitive development, and incidence of adverse events).	Firstly, mean anthropometric indices (weight-for-height, height-for-age, head circumference-for-age) will be compared across three groups using independent t-tests. Secondly, adverse events (overall morbidity) by the end of follow-up will be compared across the three groups using Chi-squared tests. Age-standardised CREDI summary scores (z-scores) analysed as continuous outcomes, reported as adjusted mean differences with 95% confidence intervalsUsing linear regression, we will assess whether breast milk CAB concentrations predict growth patterns and morbidity, adjusting for infant age, sex socio-economic status, birth weight and gestation age at birth. Random effects models will account for intra- and interindividual variability in repeated measurements. Exploring this analysis may inform algorithms for monitoring CAB safety signals in infants. These algorithms could be validated in larger studies and incorporated into routine practice for early detection of CAB-related risks in infants.	Impact of CAB breast milk exposure on infant growth and neurocognitive development in comparison to the standard daily oral PrEP.

This table outlines each primary and secondary study objective alongside the corresponding outcomes, exposure measures, and planned statistical or pharmacokinetic analyses. It summarises how each objective will be addressed analytically, including comparisons across maternal PrEP exposure groups and evaluation of infant pharmacokinetic, safety, growth, and developmental outcomes.

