## Main and specific objectives of the CABMILK study

The broad objective of the CABMILK Study is:
•To characterise cabotegravir transfer into breastmilk and the resulting infant exposure among breastfeeding women receiving long-acting injectable cabotegravir for HIV pre-exposure prophylaxis, and to describe, in a preliminary, non-inferential manner, the infant safety, growth, and developmental patterns in this group relative to infants whose mothers receive oral PrEP (TDF/FTC) or no PrEP.

The specific aims of the study are:
•To evaluate the extent of cabotegravir transfer into breast milk and determine its pharmacokinetics in infants who are breastfed by mothers receiving long-acting injectable cabotegravir for HIV PrEP.•To describe the pattern of infant safety, growth, and developmental outcomes over eight months of follow-up among infants exposed to cabotegravir through breastmilk, those exposed to oral TDF/FTC through breastmilk, and PrEP-naïve infants, with effect sizes and 95% confidence intervals reported without formal between-group hypothesis testing

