### Step 2-
Cabotegravir safety, growth pattern and development study

We hypothesise that there will be no difference in the incidence of adverse events or illnesses, growth, and development between infants exposed to breast milk CAB and those exposed to breast milk oral PrEP. 25 mother-infant pairs from Step 1 (mothers receiving CAB for PrEP), 25 other mother-infant pairs from the oral PrEP group of the PathToScale and LINK studies and 50 mother-infant pairs naïve of PrEP, matched to those in the CAB PrEP group, will be followed up for eight months from the time of maternal PrEP initiation in the PrEP groups or a similar time in the PrEP naïve group. The PathToScale and LINK studies are following up mothers in the CAB group from the initiation visit, 1 month later and, thereafter, every 2 months. In our study we will follow a similar schedule for all three groups with a final exit visit scheduled at eight months post initial CAB dose. This will result in 10 scheduled visits in the CAB group and six in the oral PrEP and no PrEP groups. The CAB LA PrEP group will have four additional visits for PK sampling at month 7. In the present CABMILK Study, we will utilise all six planned visits to assess the incidence of reported adverse events and infant growth by measuring anthropometric indices (weight-for-height and height-for-age) as well as head circumference-for-age. The same visit schedule and safety assessments will be applied to the oral PrEP and PrEP-naïve groups. Infant growth and neurodevelopment will be longitudinally assessed at all six study visits using the Caregiver Reported Early Development Instrument (CREDI).

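### Table 2 orders t-tests on growth and chi-squared tests on adverse events between groups, which the aims and the analysis text rule out

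*Protocol article*

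**What the plan says.** The section on main and specific objectives sets out, in the broad objective, "to describe, in a preliminary, non-inferential manner, the infant safety, growth, and developmental patterns in this group". The second specific aim says that infant safety, growth and development will be described "with effect sizes and 95% confidence intervals reported without formal between-group hypothesis testing".

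The Data analysis section makes the primary safety results descriptive, "without group-comparison p-values". It leaves between-group inference on safety to larger studies and analyses growth and CREDI with mixed-effects models adjusted for infant age, sex and site. The sample size section says that Step 2 was not designed for formal comparisons, and the Limitations concede that power for group differences is lacking.

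Table 2, which the Data analysis section introduces as the outline of the planned analyses, reads differently. Under its second objective it says that "mean anthropometric indices (weight-for-height, height-for-age, head circumference-for-age) will be compared across three groups using independent t-tests", and then that "adverse events (overall morbidity) by the end of follow-up will be compared across the three groups using Chi-squared tests".

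Step 2 opens with a hypothesis about infants exposed to CAB and infants exposed to oral PrEP through breast milk: "We hypothesise that there will be no difference in the incidence of adverse events or illnesses, growth, and development".

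**The concern.** For growth and adverse events the article states two analyses that cannot both be followed. An analyst working from Table 2 would produce unadjusted p-values between self-selected groups. An analyst working from the text would produce estimates with intervals and no p-values. If this stays open, the choice can be made after the results are seen.

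The t-test is also a poor choice on its own terms. It compares two groups, so a comparison across three implies pairwise tests whose number and handling are not stated. It adjusts for nothing, while the text calls for adjustment because women choose their own exposure group.

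The hypothesis of no difference adds to this. With 25 infants in each exposed group, a non-significant test is likely even when a moderate difference exists, and it could be taken to confirm the hypothesis. The results are meant for the Ministry of Health and the national rollout, so the distinction matters.

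**Working it through.** The plan gives no alpha, effect size or power for Step 2, so there is no figure of its own to reproduce. The check sets the texts side by side and then illustrates the size of the problem.

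**Texts compared**

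| Outcome | Aims and Data analysis text | Table 2 |
|---|---|---|
| Growth indices | Effect sizes with 95% intervals, no formal tests; adjusted mixed-effects model | Independent t-tests, three groups |
| Adverse events | No formal tests; descriptive, no group p-values | Chi-squared tests, three groups |
| CREDI | Adjusted mixed-effects model | Adjusted mean differences with 95% intervals |

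The first two rows conflict and the third does not. The exclusion of p-values is worded for safety results. For adverse events the table therefore contradicts both the aim and the Data analysis text. For growth it contradicts the aim and the mixed-effects model.

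**Number of t-tests.** Inputs are three indices (Table 2) and three groups, hence three pairs: 3 × 3 = 9 tests at one time point. The chi-squared test can handle three groups at once, so this count concerns growth only.

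**False positives.** Assume a two-sided 0.05 per test and no true differences.
- If the nine tests were independent: 1 − 0.95^9 = 0.370.
- They are not independent, because the pairs share groups. A simulation of 20,000 runs with normal data and groups of 25, 25 and 50 gives 0.324 with uncorrelated indices and 0.283 with a correlation of 0.5 between indices.

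**What the tests could detect** (same alpha)
- t-test power for a 0.5 SD difference: 41% (25 v 25) and 52% (25 v 50).
- Difference detectable with 80% power: 0.81 SD (25 v 25) and 0.70 SD (25 v 50).
- Power for adverse event risks of 20% v 40% (assumed): 33% (25 v 25) and 46% (25 v 50).
- Expected events in a group of 25 are 25 × p. This falls below 5 when the overall risk p is under 0.20, where the chi-squared approximation is weak.

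**Precision if only estimates are reported.** The 95% half-width for an unadjusted mean difference at one time point is:
- 25 v 25: t(0.975; 48) × √(1/25 + 1/25) = 2.011 × 0.283 = 0.57 SD
- 25 v 50: t(0.975; 73) × √(1/25 + 1/50) = 1.993 × 0.245 = 0.49 SD

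These power and precision figures follow from the sample size, and rewording the table does not change them. They show why estimates with intervals suit this design better than tests.

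**The case against.** The best defence is that the descriptive intent is plain. The aims, the sample size section, the Data analysis text and the Limitations all say so, comparative analyses are called exploratory, and results are to stress effect sizes and intervals and be read with caution. On that view, one table cell is a leftover that would mislead nobody. The descriptive intent is indeed clear, which makes the fix easy. It does not remove the conflict, because the text excludes the tests and p-values themselves, and Table 2 is named as the plan. The word primary before the safety results might leave room for secondary tests, but the second aim excludes formal testing without that qualifier.

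Other points on that side stand and limit the concern:
- A reader might infer that Table 2 ignores repeated measures altogether. It does not. The same cell mentions random effects models for repeated measurements, although it does not say that they replace the t-tests.
- A reader might infer that CREDI is tested as well. Table 2 gives adjusted mean differences with intervals for CREDI, in line with the text.
- A reader might multiply nine tests by six visits to get 54 tests and a false-positive chance near 94%. No section says that the t-tests are repeated at each visit, and that figure needs 54 independent tests, which shared groups and repeated infants rule out.
- Confounding is not wholly unaddressed. Step 2 says that the PrEP-naïve pairs are matched to the CAB pairs. That helps one of the three comparisons, though an independent t-test makes no use of the matching.
- Nothing says that a non-significant result will be presented as reassurance. That is a risk created by the wording of the hypothesis, not a stated plan.

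**Conclusion.** The contradiction is real, and it covers growth and adverse events only. Table 2 prescribes formal tests that the second aim excludes. For adverse events it also conflicts with the bar on group p-values, and for growth with the adjusted mixed-effects model. Followed literally for growth, it leads to nine unadjusted pairwise tests at a single time point, with roughly a 28–32% chance of at least one false positive and an upper bound of 37%. These figures assume 0.05 per test, normal data, no true differences and complete groups of 25, 25 and 50.

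It affects a secondary objective that is declared exploratory. The primary pharmacokinetic analysis is untouched. A reader might extend the point to the sentence in the same cell that says "we will assess whether breast milk CAB concentrations predict growth patterns and morbidity". That regression is not a comparison between groups, so the exclusion of between-group tests does not bear on it and nothing is concluded about it here.

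**What to change.** - Delete the independent t-tests and the chi-squared tests from Table 2.
- For growth, state that adjusted mean differences with 95% intervals will come from the mixed-effects model in the Data analysis section.
- Settle one covariate list for that model. The Data analysis section names infant age, sex and site. The sample size section promises maternal as well as infant confounders. Table 2 lists age, sex, socio-economic status, birth weight and gestational age for its regression. The exclusion criteria section also says that gestational age will be a covariate.
- For adverse events, report counts, proportions with exact 95% intervals and incidence rates by group, without p-values.
- Reword the no-difference hypothesis in Step 2 as a descriptive aim, and add that an interval including zero will not be presented as evidence of no difference.

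The cost is one table cell, one hypothesis sentence and agreement on the covariates. The methods are already in the article, and no extra visits or samples are needed. Enrolment is under way, so the change should be made before any comparative results are seen.

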**Figure 2. f2:**
[figure not shown]
Pharmacokinetic sampling schedule for the CABMILK study. Timeline of maternal plasma, breastmilk, and infant dried blood spot (DBS) sample collection used to characterize cabotegravir pharmacokinetics and infant exposure during breastfeeding. The sparse PK sampling visit occurs at month 7 after enrolment, corresponding to the fifth CAB-LA injection, after participants have received four prior injections. This schedule enables estimation of maternal drug concentrations, milk-to-plasma ratios, and infant exposure metrics.

**Table 1. T1:** Schedule of study procedures and sample collection in the CABMILK study.

Visit description											
Visit number	1	2	3	4	5	6	7	8	9	10	Unscheduled
Visit month	0	1	3	5	7	7	7	7	7	8	Any
Visit study time	Pre- dose	Pre- dose	Pre- dose	Pre- dose	Pre-dose (0 hr)	24 hr	Day 7±3	Day 14±3	Day 28±5	Study exit	Sick visit
Screening and enrolment											
Informed consent discussion	x										
Medical and drug history	x										x
Revision of eligibility criteria	x										
ID number assignment	x										
Capillary haemoglobin measurement	x				x						
Group A: Mother-infant pairs on cabotegravir PrEP											
General physical examination	x	x	x	x	x	x	x	x	x	x	x
Recording of current and concomitant medication	x	x	x	x	x	x	x	x	x	x	x
Anthropometric measurements to assess growth ^#^	x	x	x	x	x					x	
Cognitive and neuro-assessment using a validated tool such as MDAT or equivalent	x	x	x	x	x					x	
Adverse events assessment	x	x	x	x	x	x	x	x	x	x	
Maternal venous blood PK sample					x		x				
Mandated breastmilk feeding or record of latest time of feeding*							x				
Maternal breastmilk PK sample					x		x				
Infant capillary blood PK sample					x	x	x	x	x		
Infant feeding patterns and record of any food supplementation	x	x	x	x	x	x	x	x	x	x	x
Groups B & C: Mother-infant pairs in oral PrEP group and PrEP naïve											
General physical examination	x	x	x	x	x					x	x
Recording of current and concomitant medication	x	x	x	x	x					x	x
Anthropometric measurements to assess growth ^#^	x	x	x	x	x					x	
Cognitive and neuro-assessment	x	x	x	x	x					x	
Adverse events assessment	x	x	x	x	x					x	

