^ post-dose. The latter will be achieved by aiming to mandate a feed at the expected maternal peak and then sampling 1 hour later or, where mandated feeding is not possible, collecting information on the time of last infant breastfeeding. We will further collect infant capillary blood samples at 24 hours then 7 (±3), 14 (±4) and 28 (±5) days post maternal CAB dosing, resulting in five infant sampling occasions (
Figure 2). The collected blood sample will be applied on two dry blood spot (DBS) filter papers (Whatman 3MM) and left to dry. The DBS filter papers for each participant will be stored, with desiccant, in sealed zipper plastic bags to ensure that they do not pose any potential biological hazards. They will be stored at room temperature at a collaborating institution, the University of North Carolina (UNC)’s laboratory before shipment to assay cabotegravir concentrations. The remaining samples will be archived at Malawi-Liverpool-Wellcome Programme (MLW)’s laboratory in Blantyre.

Ideally, venous plasma samples, as opposed to capillary samples, should also be collected in infants (as in the case of the mother). However, to limit the amount of infant blood sampling volume, a capillary blood sampling matrix has been opted for in the infants.

*Duration of sample storage*

All samples (breast milk and blood) will be collected in duplicate; one backup at the Malawi-Liverpool Wellcome Programme (MLW) laboratory and the other shipped for cabotegravir assay. The maximum period of sample storage at MLW (backup samples) will be five years.

*Assaying cabotegravir concentrations*

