### Risk of study participation: venous sampling, breastmilk sampling, finger/heel pricks and mitigation of potential injury

Participants will undergo repeated needle and finger/heel pricks in this study, than they normally would, but in line with standard hospital procedures in relation to blood sample collection. The risks of these procedures include pain, transient bleeding, and soft tissue infection. A small bruise or mild pain at the site from where the blood is taken may develop. To mitigate this risk, only well-trained study staff will be hired for the project. Additionally, only new disposable needles and lancets will be used for the blood collection procedures, which will be safely discarded immediately after use. Furthermore, breastmilk manual expression, as part of sampling, may be associated with some minimal risk of discomfort in mothers and the need for privacy. To mitigate this, all mothers will be supported by trained study team members to manually express breastmilk comfortably. In addition, all sampling occasions will be conducted in a private room/space to ensure comfort and maintain privacy.

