### Recommended infant blood sample volume

Infant blood will be collected using calibrated micro-collection EDTA tubes, and each infant will contribute five blood samples (
Figure 2). The total infant blood volume will not exceed 5 mL for all blood sampling time points. This volume is safe for an infant as per NIHR guidelines that state that that blood volume limits for sampling, per individual (including study-related blood loss and any losses in the manoeuvre), should not exceed 3% of the total blood volume in a period of four weeks, and should not exceed 1% at any single time. For a 5 kg infant, this equates to 4 mL per sample/at a single sampling time point or 12 mL over 4 weeks.
^
20
^ A total infant blood volume of 5 mL for all blood sampling time points in the CABMILK study is therefore safe. In all study procedures, loss of blood or excess blood sample collection will be minimized, during sampling, by using calibrated capillary and venous collection tubes.

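### Infant PK pricks are scheduled only in the CAB-LA group, and nothing shown keeps sampling-site reactions apart from the adverse events compared across groups

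*Protocol article*

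**What the plan says.** Table 2 (Data analysis, second objective) sets the safety comparison: "adverse events (overall morbidity) by the end of follow-up will be compared across the three groups", using Chi-squared tests. The Data analysis text gives the form of reporting: "Primary safety results will be descriptive: counts, proportions with exact 95% confidence intervals, incidence rates, and Kaplan–Meier curves", without p-values between groups.

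Step 1 describes the infant sampling as pre-dose, 24 hours, and about days 7, 14 and 28 after the fifth maternal dose, "resulting in five infant sampling occasions". In Table 1 the row "Infant capillary blood PK sample" stands in the Group A block and is marked at visits 5 to 9. The block headed "Groups B & C: Mother-infant pairs in oral PrEP group and PrEP naïve" has no blood-sampling row. The section on infant blood volume says that "each infant will contribute five blood samples" without naming a group, but Table 1 and Step 1 place these samples in the CAB-LA group.

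On harms of sampling, the risk section states: "The risks of these procedures include pain, transient bleeding, and soft tissue infection". It adds that a small bruise or mild pain may develop where blood is taken.

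The article does not say how an event caused by study sampling is classified or reported.

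**The concern.** The safety outcome is worded to cover all adverse events, while one recognised source of minor adverse events is a research procedure carried out in one group only. In the infants, PK sampling and CAB-LA group membership coincide completely. Covariate adjustment therefore cannot separate them. Dropping p-values does not help either, since counts, proportions, rates and curves carry the same imbalance.

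The timing makes it harder to read. All five pricks fall between month 7 and about month 8, around the fifth dose and the expected maternal peak. Any reactions would appear as a late fall in the CAB-LA Kaplan–Meier curve, where a reader would look for an effect of exposure. The Discussion offers the findings as early safety signals, and the dissemination plan intends algorithms for detecting safety concerns in exposed infants. A procedural contribution to the CAB-LA event count would be unwelcome in both.

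**Working it through.** **The plan's own figures.** Marks for the infant PK sample in Table 1, Group A: visits 5, 6, 7, 8 and 9, which is 5 and agrees with Step 1. Groups B and C: 0. With the planned group sizes of 25, 25 and 50:

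- CAB-LA: 25 × 5 = 125 planned PK pricks
- oral PrEP and PrEP-naïve: 75 × 0 = 0

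**Assumptions.** The article gives neither a reaction rate per prick nor the proportion of infants expected to have any adverse event in eight months. Let q be the probability of a recorded local reaction per prick (1% to 10% assumed). Let p be the background proportion of infants with any event (20% and 80% assumed). Reactions are taken as independent of each other and of background illness, every planned prick is done, and every reaction is counted as an adverse event.

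**Formulas.**

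- Infants with at least one sampling event: 1 − (1 − q)^5
- Expected number of sampling events: 125q
- Rise in the CAB-LA proportion with any event: [1 − (1 − p)(1 − q)^5] − p = (1 − p)[1 − (1 − q)^5]

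Example, q = 2%: 1 − 0.98^5 = 9.6%. At p = 20% the rise is 0.80 × 9.6 = 7.7 points; at p = 80% it is 0.20 × 9.6 = 1.9 points.

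| q per prick | Infants with ≥1 sampling event | Expected events (125q) | Rise in any-event proportion, p = 20% | Rise, p = 80% |
|---|---|---|---|---|
| 1% | 4.9% | 1.3 | 3.9 points | 1.0 points |
| 2% | 9.6% | 2.5 | 7.7 points | 1.9 points |
| 5% | 22.6% | 6.3 | 18.1 points | 4.5 points |
| 10% | 41.0% | 12.5 | 32.8 points | 8.2 points |

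In infants out of 25, the rise runs from 1.0 to 8.2 at p = 20% and from 0.2 to 2.0 at p = 80%. Background illness dilutes the proportion with any event. It does not dilute counts and rates of events, where all 125q extra events fall in one group.

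**The Chi-squared test in Table 2.** Simulation with groups of 25, 25 and 50, no drug effect, 2 degrees of freedom, 5% level and 40,000 runs gave these rejection rates for q = 1%, 2%, 5% and 10%:

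- p = 20%: 6.6%, 10.7%, 35.2%, 79.4%
- p = 80%: 4.8%, 4.9%, 5.9%, 10.0%

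With q = 0 the rate was 4.7% to 5.1% across the backgrounds tried (20% to 80%).

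**Would common visits remove it?** Step 2 speaks of using six planned visits for adverse-event incidence, while Table 1 marks adverse-event assessments at ten visits for Group A and six for Groups B and C. Four of the five pricks fall at the extra visits, so a restriction to common visits would narrow the route. It need not close it: the pre-dose prick is at visit 5, a common visit, and the common month-8 exit visit comes close to the day-28 prick.

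**Other pricks.** The row "Capillary haemoglobin measurement" (visits 1 and 5) stands above the group blocks and does not say whether mother or infant is tested. If infants in all groups have it, the comparison infants are not free of pricks, but the difference of five PK pricks remains.

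**The case against.** The strongest objection is that this rests on silence. The article does not define an adverse event or say how procedure-related events are handled. Such rules are commonly left to the full protocol, the SAP and the case report forms; the article says that a SAP and sample collection forms exist, and they are not shown. This stands as a limit on the claim. A reader might infer that sampling injuries would count and would be ascribed to cabotegravir. The document does not support that. It supports only that they could count, because the stated outcome is all-inclusive and nothing shown separates them.

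Second, morbidity may mean illness, and a heel-prick bruise may never be recorded. This stands in part. However, the Step 2 hypothesis names adverse events alongside illnesses, and soft tissue infection, which the article lists, is an illness on any reading. That risk list also covers maternal venepuncture, so it is not a list of infant harms alone.

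Third, a reader might infer that a 2% reaction rate adds nearly 10 points to the CAB-LA group. That 9.6% is the share of infants with a sampling event. It equals the rise in infants with any event only if no infant has any other event in eight months. The article describes these infants as at higher risk of general childhood illness, so a background near zero is unlikely.

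Fourth, leaving out attributed events can itself bias the result. Attribution is unblinded and can remove events mainly from the CAB-LA group. This stands and shapes the fix.

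Finally, the safety analysis is declared descriptive and exploratory. That lowers the stakes but does not correct the summaries.

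**Conclusion.** The concern holds in a limited form. Five PK pricks per infant are planned in the CAB-LA group and none in the comparators, the article recognises local harms of sampling, and the compared outcome is all adverse events. Sampling-related events could therefore count against CAB-LA.

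The direction is clear but the size is not. Under the assumed range it runs from about 1 point (1% per prick, 80% background) to about 33 points (10% per prick, 20% background) in the proportion of infants with any event. Both inputs are assumptions, and the effect may be negligible in practice. It does not touch the pharmacokinetic objective. It is worth correcting because the safety signal is a stated output and the correction is cheap.

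The unequal number of adverse-event assessments (ten against six) is a separate imbalance, which this correction does not remove.

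**What to change.** 1. On the adverse-event form, in all three groups, add a field for whether the event is a local reaction at a study sampling site. Use a narrow, objective definition based on the site of the reaction and its timing after a documented sample, fixed in advance.
2. In the Data analysis section and Table 2, state that counts, proportions, rates and Kaplan–Meier curves by group will be shown side by side for all adverse events and for adverse events excluding sampling-site reactions.
3. List the sampling-site reactions separately.
4. Keep the all-events result in the main table. Because attribution is unblinded, the second result accompanies it and does not replace it.
5. State whether the capillary haemoglobin measurement is taken from mother or infant and in which groups, so that the number of infant pricks per group is known.

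The cost is one form field, one further set of summaries and one listing, plus submission of the change to the ethics committee before use, as the article requires for amendments. Recruitment began in September 2025 and the infant PK samples fall at month 7, so the first were due from about April 2026. The field is better added early than reconstructed from notes.
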